
### Sample size

A 3-point difference on our primary outcome (RTSHIA) between treatment groups represents a clinically important difference.^35^ However, we propose to adopt a more conservative approach and will power the study to detect a moderate effect representing a 2-point difference. With an SD of 3.6, 90% power, alpha set at 0.05, we will require 69 participants per group.

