**Methods and analysis:**

This study is a single-blind, randomised controlled trial comparing usual CAMHS care with usual care plus BlueIce. A total of 138 adolescents aged 12–17 with current or a history of self-harm will be recruited through the Oxford Health National Health Service (NHS) Foundation Trust via their CAMHS clinician. The primary outcome is self-harm at 12 weeks assessed using the Risk Taking and Self-Harm Inventory for Adolescents. Secondary outcomes include mood, anxiety, hopelessness, general behaviour, sleep and impact on everyday life at 12 weeks and 6 months. Health-related quality of life and healthcare resource utilisation data will be collected at baseline, 12 weeks and 6 months. Postuse interviews at 12 weeks will determine the acceptability, safety and usability of BlueIce.

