### Randomisation

Computer-generated randomisation will be independently undertaken by Exeter Clinical Trials Unit. Participants will be randomised in a 1:1 ratio to either UC or usual UC+BI. Participants will be randomised using REDCap software minimising for gender, age (over or under 16), self-harm frequency in last 4 weeks (0–2 or ≥3) and severity of depression (Mood and Feelings Questionnaire (MFQ) above or below 27, the cut-off for severe depression). Because of the nature of the intervention, participants will not be blind to their allocation. However, researchers involved in data collection will remain blind to allocation. Participant allocation will be undertaken by a member of the project team who is not involved in undertaking patient assessments.

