### Planned analysis

#### Statistical analysis

Our primary analysis will be at the end of the 12 weeks follow-up of the last recruited participant. A statistical analysis plan will be developed by the trial statistician in consultation with the project management group and agreed with the SSC before database lock. We will follow the Consolidated Standards of Reporting Trials extension for reporting RCTs and will follow recommended guidelines for analysis of our data.^52^ Our primary analysis at 12 weeks will be analysed on an intention to treat principle. Although we are not expecting a significant amount of missing data at 12 weeks, the impact of missing data will be assessed by comparing baseline covariates for missing and non-missing cases. In the event that there is evidence of bias being introduced into the analysis, then further consideration, including but not limited to multiple imputation, will be given regarding how to address this.

Descriptive statistics will summarise baseline characteristics for each arm and patterns of missing follow-up data will be explored. We will also undertake a per protocol analysis of our primary outcome, total scores on the RTSHIA. Regression analysis adjusting for baseline minimisation variables of age, gender, mood and self-harm frequency will be undertaken. We will conduct sensitivity analyses, in which we adjust for prognostic variables for which there is a baseline imbalance between intervention arms. Further sensitivity analyses will use multiple imputation to deal with missing data.

Similar regression analyses will be conducted for secondary outcomes (linear regression for numerical outcomes and logistic regression for binary outcomes). All secondary outcome measures will be compared between the groups and will include summary statistics and CIs for measures of effect size.

Analysis of the 6-month data will be included in a repeated measure analysis to investigate the maintenance of any effect seen at 12 weeks. Analysis of the 6 month follow-up data will be undertaken using a repeated measures analysis of variance with both the 12 weeks and 6-month data being included and adjusted for the baseline. The analysis will also be adjusted for the baseline minimisation variables: age, gender, mood and frequency of self-harm as proposed for the primary analysis at 12 weeks.

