### Strengths and limitations

This is the first adequately powered RCT of a digital self-help app codesigned with, and used by, young people aged 12–17 years in receipt of specialist mental health services. This study will add to the evidence-base and will document the effectiveness and cost-effectiveness of adding a self-help app to usual care. If benefits are identified, BlueIce app can be widely made available to young people attending specialist CAMHS to provide help at times of distress.

As it is not feasible to blind participants to allocation, the research team is aware of the need to maintain equipoise and to present the two interventions to referring clinicians and participants in a balanced way. Researchers will remain blind to treatment arm and, if this is inadvertently broken, subsequent assessments will be conducted by another member of the research team. Similarly, following guidance from our participation group, those allocated to usual care will be provided with BlueIce at their final, 6-month assessment.

We have minimised the possibility of contamination between the trial arms. BlueIce is a prescribed app and is not freely available to download and use. Those allocated to UC+BI will be sent a single use download code. Once activated, BlueIce will automatically be installed on the participant’s smartphone and the access code will no longer work. Participants are, therefore, unable to share/pass the app/access code to others.

Finally, this project will evaluate the use of BlueIce as a prescribed app, used in conjunction with a specialist mental health intervention. Future research will be required to evaluate the use of BlueIce as a standalone, freely accessed self-help app or the mechanisms underpinning any effects.

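### The recruitment target of 138 equals the number to be analysed (2 × 69), so the stated 90% power, for the unadjusted comparison behind it, requires complete 12-week data

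*Protocol article*

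**What the plan says.** The Sample size section of the protocol article calls a 3-point difference on the RTSHIA clinically important, then chooses a smaller target: the investigators "will power the study to detect a moderate effect representing a 2-point difference". It continues: "With an SD of 3.6, 90% power, alpha set at 0.05, we will require 69 participants per group". It mentions neither loss to follow-up nor covariate adjustment.

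The Abstract (Methods and analysis) gives the recruitment target: "A total of 138 adolescents aged 12–17 with current or a history of self-harm will be recruited". It also fixes the primary time point: "The primary outcome is self-harm at 12 weeks". The Randomisation section sets equal allocation: "Participants will be randomised in a 1:1 ratio".

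On missing data, the Statistical analysis section says "Although we are not expecting a significant amount of missing data at 12 weeks". It then plans to compare baseline covariates between missing and non-missing cases, to consider multiple imputation if there is evidence of bias, and to use multiple imputation in sensitivity analyses. It also plans regression adjusted for the minimisation variables: age, gender, mood and self-harm frequency.

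The Strengths and limitations section of the Discussion claims: "This is the first adequately powered RCT of a digital self-help app".

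**The concern.** The number to be recruited and the number that must be analysed are the same. A sample size with no allowance for loss gives its stated power only if every randomised participant provides the primary outcome. The protocol does not say that its 90% carries this condition, and its own missing-data plan allows for some loss. A reader of the Sample size section would take 90% as the power of the trial as it will be run, when it is the power with complete data.

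Power and detectable difference are what a reader uses to judge a null result. If the stated power is somewhat too high, a null result at 2 points looks somewhat more conclusive than it is.

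**Working it through.** **Inputs.** Difference 2 points, SD 3.6, power 90%, alpha 0.05 and 69 per group (Sample size); 138 recruited (Abstract); 1:1 allocation (Randomisation). The protocol does not say whether alpha is one- or two-sided, and it gives no loss rate.

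**Step 1: reproduce the plan's figure.**

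n per group = 2 × (z₀.₉₇₅ + z₀.₉₀)² × (SD/difference)² = 2 × (1.960 + 1.2816)² × (3.6/2)² = 68.09, rounded up to 69.

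The two-sample t-test gives 69.06. One-sided alpha would need only 56. So 69 is the two-sided, unadjusted number analysed, with no inflation.

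**Step 2: look for slack.** 2 × 69 = 138, the recruitment target. Power by the t-test is 89.97% at 69 per group and 89.5% at 68. The only margin is rounding.

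**Step 3: power after loss.** The loss rates are assumptions. Completers per group are 69 × (1 − loss), rounded to a whole number. Power is for a two-sided t-test at standardised difference 2/3.6 = 0.556.

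| Assumed loss | Completers per group | Power for 2 points | Difference detectable with 90% power |
|---|---|---|---|
| 0% | 69 | 90.0% | 2.00 |
| 5% | 66 | 88.6% | 2.05 |
| 10% | 62 | 86.6% | 2.11 |
| 15% | 59 | 84.9% | 2.17 |
| 20% | 55 | 82.3% | 2.25 |
| 25% | 52 | 80.1% | 2.31 |

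**Step 4: what covariate adjustment could give back.** If the covariates explain a share R² of the outcome variance, the residual SD is 3.6 × √(1 − R²). The protocol does not report R², so these values are also assumptions.

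| Assumed R² | Completers per group | Power for 2 points |
|---|---|---|
| 5% | 66 (about 5% loss) | 90.2% |
| 10% | 62 (10% loss) | 89.9% |
| 15% | 59 (15% loss) | 90.1% |
| 20% | 55 (20% loss) | 89.8% |

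As a rule of thumb, the share of variance explained must roughly match the share of participants lost.

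**Step 5: power for the 3-point difference.** With SD 3.6 and no adjustment, power for 3 points is 99.6% at 62 per group, 99.1% at 55 and 98.8% at 52.

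**The case against.** The strongest reply is that nothing in the Sample size section is miscalculated, that the protocol does state a retention expectation, and that its missing-data plans are ordinary contingencies which do not concede substantial loss. All of this stands. What remains is that the expectation has no number, and that not expecting a significant amount is not the same as expecting none.

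The second reply is that the planned regression adjusts for baseline self-harm frequency and mood, and the sample size takes no credit for this. That also stands as a possibility. How large the gain would be is unknown. In the minimisation these variables are two-level factors (self-harm frequency 0–2 or ≥3; MFQ above or below 27), and if they enter the model in that form they carry less information than full scores. The protocol neither states nor relies on a gain. Multiple imputation is not a substitute, since it does not in general restore the information lost with missing primary outcomes.

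Three stronger readings are tempting, and the document does not support them:

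- A reader might infer that 90% power is out of reach under any realistic retention. Step 4 shows that a modest covariate effect could offset a 10% loss, so this does not follow.
- A reader might infer that the claim of adequate power is false. Unadjusted power stays at or just above 80% up to 25% loss, and the detectable difference stays below the protocol's own 3-point threshold, so it is not.
- A reader might infer that adding the baseline RTSHIA total to the model would recover most or all of the loss. That depends on a correlation between baseline and outcome that the protocol does not report.

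**Conclusion.** The point holds as a matter of sample-size assumptions. The target of 138 contains no allowance for loss, so the stated 90% power for 2 points requires complete 12-week data on the unadjusted comparison that produced the figure. No other section supplies an allowance. Because 138 follows exactly from the stated inputs, none can be hidden in it.

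The size is moderate: about 1 percentage point of power at 5% loss, 3 at 10%, 8 at 20% and 10 at 25%. These figures rest on assumed loss rates, the protocol's SD of 3.6 and no covariate gain. For the 3-point difference that the protocol calls clinically important, power stays near 99% across this range, so the risk of over-reading a null result is confined to effects of around 2 points. The text should be corrected, but the design is not undermined.

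**What to change.** Restate the Sample size section along these lines:

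*A total of 138 randomised (69 per group) gives 90% power to detect a 2-point difference (SD 3.6, two-sided alpha 0.05) only if 12-week outcomes are complete. We expect [x]% loss by 12 weeks, which leaves [n] per group and gives [p]% power for an unadjusted comparison.*

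The investigators supply x. As a guide, 10% to 20% loss gives about 87% to 82%. If they wish to count on the planned covariate adjustment, they should state the assumed share of variance explained and where that figure comes from.

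The claim of adequate power in Strengths and limitations may stand if the power it refers to is given beside it.

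The cost is a few sentences and a slightly less favourable stated power. Recruitment, design and analysis are unchanged.

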### Planned analysis

#### Statistical analysis

Our primary analysis will be at the end of the 12 weeks follow-up of the last recruited participant. A statistical analysis plan will be developed by the trial statistician in consultation with the project management group and agreed with the SSC before database lock. We will follow the Consolidated Standards of Reporting Trials extension for reporting RCTs and will follow recommended guidelines for analysis of our data.^52^ Our primary analysis at 12 weeks will be analysed on an intention to treat principle. Although we are not expecting a significant amount of missing data at 12 weeks, the impact of missing data will be assessed by comparing baseline covariates for missing and non-missing cases. In the event that there is evidence of bias being introduced into the analysis, then further consideration, including but not limited to multiple imputation, will be given regarding how to address this.

Descriptive statistics will summarise baseline characteristics for each arm and patterns of missing follow-up data will be explored. We will also undertake a per protocol analysis of our primary outcome, total scores on the RTSHIA. Regression analysis adjusting for baseline minimisation variables of age, gender, mood and self-harm frequency will be undertaken. We will conduct sensitivity analyses, in which we adjust for prognostic variables for which there is a baseline imbalance between intervention arms. Further sensitivity analyses will use multiple imputation to deal with missing data.

Similar regression analyses will be conducted for secondary outcomes (linear regression for numerical outcomes and logistic regression for binary outcomes). All secondary outcome measures will be compared between the groups and will include summary statistics and CIs for measures of effect size.

Analysis of the 6-month data will be included in a repeated measure analysis to investigate the maintenance of any effect seen at 12 weeks. Analysis of the 6 month follow-up data will be undertaken using a repeated measures analysis of variance with both the 12 weeks and 6-month data being included and adjusted for the baseline. The analysis will also be adjusted for the baseline minimisation variables: age, gender, mood and frequency of self-harm as proposed for the primary analysis at 12 weeks.

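### The stated 12-week primary model does not name baseline RTSHIA total as a covariate: a free gain in precision, not a flaw that invalidates the trial

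*Protocol article*

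**What the plan says.** Under Statistical analysis, the protocol article gives the covariates of the 12-week regression: "Regression analysis adjusting for baseline minimisation variables of age, gender, mood and self-harm frequency will be undertaken". That sentence comes straight after one on a per-protocol analysis. However, the closing paragraph of the section refers back to the same four variables as those proposed for the 12-week primary analysis, so the list does describe the primary model.

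The self-harm variable on the list comes from Randomisation, where the minimisation factor is "self-harm frequency in last 4 weeks (0–2 or ≥3"). The outcome is a different measure. Under Part B: RTSHIA it is the sum of 18 items scored 0 to 3, so it runs from 0 to 54. It is collected at baseline over a 6-month recall period and at each follow-up over 3 months.

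Two other analyses in the same section bear on the point:
- The repeated-measures analysis has both the 12-week and 6-month data "being included and adjusted for the baseline", and is in addition adjusted for the minimisation variables.
- Sensitivity analyses will "adjust for prognostic variables for which there is a baseline imbalance between intervention arms".

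**The concern.** The baseline value of a score is often among the strongest predictors of its later value. A two-level count over 4 weeks differs from the RTSHIA total in content, recall period and resolution, so it can stand in for that total only in part. The protocol treats the two as distinct, since the repeated-measures analysis takes the baseline and then also the minimisation variables.

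At stake are the width of the primary confidence interval and the share of any chance difference in baseline severity that stays in the primary estimate. There is also a point of consistency. The same 12-week data would be analysed once without and once with the baseline score, so the report could carry two 12-week estimates that differ for no stated reason.

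**Working it through.** **Inputs from the protocol.** Sample size: "will power the study to detect a moderate effect representing a 2-point difference", and "With an SD of 3.6, 90% power, alpha set at 0.05, we will require 69 participants per group". Allocation is 1:1, and the total of 138 equals 2 × 69.

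**Assumptions, not in the protocol.** (a) r, the correlation between baseline and 12-week RTSHIA, is 0.4 to 0.7. (b) The minimisation factors explain about 12% of the 12-week variance. (c) Once baseline RTSHIA is in the model, total explained variance is r², with nothing further credited to the factors. (d) For the imbalance calculation, the baseline SD is also 3.6.

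**1. The protocol's own figure.** Two-sided, unadjusted: n per group = 2 × [(1.960 + 1.282) × 3.6 / 2]² = 68.1, which rounds up to 69. Power at 69 per group from the noncentral t is 90.0%. The stated figure reproduces and does not rely on any covariate.

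**2. Power under the plan as written.** The right comparator is the model with the four minimisation variables. Residual SD = 3.6 × √(1 − 0.12) = 3.38, and power at 69 per arm is 93.2%.

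**3. Power with baseline RTSHIA added.** Residual SD = 3.6 × √(1 − r²). The further fall in residual variance is 1 − (1 − r²)/0.88.

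| r | Residual SD | Further fall in residual variance | Power at 69 per arm |
|---|---|---|---|
| 0.4 | 3.30 | 5% | 94.2% |
| 0.5 | 3.12 | 15% | 96.3% |
| 0.6 | 2.88 | 27% | 98.2% |
| 0.7 | 2.57 | 42% | 99.5% |

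The gain over the plan is therefore about 1 to 6 percentage points of power.

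**4. Lower r.** At r = 0.3, r² is 9%, below the assumed 12%, so assumptions (b) and (c) cannot be used together. An alternative treats the frequency factor as a median split of a variable that correlates c = 0.4 to 0.8 with baseline RTSHIA and predicts the outcome only through it. The split multiplies that correlation by 0.798, so the factor explains (0.798 × c × r)² of the variance. At r = 0.3 the further fall in residual variance is then 5.5% to 8.2%, and power by the normal approximation goes from 90.6–91.4% to 92.8%. The gain is small but not nil.

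**5. Chance imbalance.** The SE of a baseline difference is 3.6 × √(2/69) = 0.61 points, and 1.96 SE is 1.20 points. Only r times a baseline difference carries into the outcome: 0.4 × 1.20 = 0.48 to 0.7 × 1.20 = 0.84 points, or 24% to 42% of the 2-point target. This gives no credit to the minimisation factors. Crediting the frequency split as in step 4 multiplies the figure by √(1 − (0.798c)²). At r = 0.5, that takes 0.60 points down to 0.46–0.57.

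**The case against.** The strongest reply is that nothing here is invalid. Leaving out a baseline covariate does not bias a randomised comparison on average, and the sample size was set without one. The gain is an efficiency not taken. All of that stands.

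A second reply is that the article is condensed, never calls its list exhaustive, and says an analysis plan will be agreed before database lock. This lowers the weight of the point but does not remove it. The article does name the covariates of the primary model, and it names the baseline separately for another analysis. An analysis plan that adds baseline RTSHIA would improve on the published list and should say so.

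A reader might infer several stronger things that the protocol does not support:
- *That baseline RTSHIA can enter only if an imbalance is observed.* It also enters the repeated-measures model with no such trigger, though not in the primary estimate.
- *That baseline imbalance goes uncorrected.* Minimising on and adjusting for self-harm frequency and mood removes part of it.
- *That power rises from 90% to 94% or more.* The 90% assumes no adjustment, whereas the plan adjusts for four variables.
- *That a 1.2-point baseline difference distorts the result by 1.2 points.* Only r times that amount carries over, and 1.96 SE is an extreme draw.
- *That the primary result depends on covariates chosen from the data.* The imbalance-based adjustment is labelled a sensitivity analysis and leaves the primary estimate alone.

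**Conclusion.** The point holds as a free improvement. The stated primary model does not name baseline RTSHIA total, although the score is collected and the repeated-measures analysis adjusts for the baseline. The cost is lost precision and only partial correction of chance imbalance in baseline severity.

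On the assumptions above (r = 0.4 to 0.7, 12% explained by the minimisation factors), adding the score cuts residual variance by a further 5% to 42% and takes power at 69 per arm from about 93% to 94–99.5%. A 1.96-SE baseline imbalance would carry about 0.5 to 0.8 points into the estimate before any credit for the minimisation factors, if the baseline SD is also 3.6.

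None of r, the 12% or the baseline SD is in the protocol. The different recall periods, 6 months at baseline and 3 at follow-up, may lower r and so shrink the gain. The trial's validity and its stated sample size are not in question.

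**What to change.** In the analysis plan, before database lock, prespecify the primary model as RTSHIA at 12 weeks regressed on arm, baseline RTSHIA total (continuous) and the minimisation variables. This matches the repeated-measures model. Note briefly that it extends the covariate list in the protocol article.

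Adjust each numerical secondary outcome for its own baseline value. Keep any adjustment prompted by observed imbalance as a sensitivity analysis only, preferably with a covariate list fixed in advance. Whether age and mood enter as continuous or in their minimisation categories is a matter of preference and not part of this point.

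The cost is wording. The protocol already schedules the baseline measures, so no extra data or participants are needed.
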